### 2.7. Outcomes

**Primary outcome**. Change in SC-CII total (0–100) from T0 to T3 (12 months), with domain-specific analyses (maintenance, monitoring, and management). An ≥8-point increase is treated as clinically important.

**Secondary outcomes**. Change in disease-specific self-care (SCHFI/SCODI/SCCOPD), HRQoL (EQ-5D-5L index and VAS; SF-36 PCS/MCS), perceived social support (MSPSS), and engagement/satisfaction with the digital education (brief evaluation form anchored to established telehealth assessment domains).

### 2.8. Statistical Analysis

Analyses will be conducted in R studios version 4.4.0. (R Foundation for Statistical Computing, Vienna, Austria; https://www.r-project.org). We will summarize baseline characteristics using means (SD) or medians (IQR) and frequencies (%). Normality will be assessed with Shapiro–Wilk tests and Q–Q plots.

**Primary analysis**. Within-subject change over time will be evaluated using repeated-measures ANOVA (or Friedman for non-normal data) on SC-CII total and domains. When the omnibus test is significant, we will perform timepoint contrasts with Bonferroni-adjusted *p*-values. We will report mean differences with 95% confidence intervals and effect sizes (partial η^2^ and Cohen’s d for pairwise changes) [30].

**Secondary analyses**. Analogous repeated-measures models will be applied to disease-specific self-care, EQ-5D-5L, SF-36 (PCS/MCS), and MSPSS. Subgroup analyses will examine differences by diagnosis (COPD vs. T2DM vs. CVD) and baseline digital literacy strata (derived from a short digital-skills screener). Multivariate linear regression will explore predictors of 12-month improvement (ΔSC-CII total), including age, sex, education, diagnosis, baseline score, and digital engagement metrics (attendance, completion time, and message interactions). Collinearity will be checked via the variance inflation factors.

**Missing data**. We will evaluate missingness patterns with Little’s MCAR test. If data are missing at random, we will apply multiple imputation (m = 5–10 datasets), including all variables used in the analysis models. Sensitivity analyses will compare imputed vs. complete-case results to assess robustness.

**Reliability**. Internal consistency will be assessed at each timepoint using Cronbach’s α, with α ≥ 0.70 considered acceptable [31].

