The COVID-19 pandemic accelerated the adoption of telehealth and digital education, revealing their potential to sustain continuity of care and support behavioral change at scale [9,10]. International experiences—particularly in the UK and Scandinavian countries—show that community nurses can effectively lead digital self-management programs, improving patient engagement and outcomes [11,12]. In Italy, the Piano Nazionale di Ripresa e Resilienza (PNRR)—Missione 6 “Salute” places the Family and Community Nurse (FCN) at the center of territorial, digitally supported chronic care. However, robust longitudinal evaluations of theory-driven, nurse-led digital education within this new framework are lacking [13,14].

PROSELF is designed to fill this gap. The intervention is explicitly theory-based [5], complemented by behavioral frameworks—Bandura’s Self-Efficacy and the Health Belief Model—to strengthen motivational components and perceived benefits/barriers [5,15,16].

Both theoretical frameworks were selected for their complementary relevance to behavioral change in chronic disease self-management. Bandura’s Self-Efficacy Theory emphasizes that individuals’ belief in their capability to execute specific behaviors directly influences persistence, motivation, and long-term adherence—constructs particularly relevant to medication routines, symptom monitoring, and help-seeking behaviors. The Health Belief Model (HBM), on the other hand, explains how perceived risk, benefits, and barriers influence health decisions and engagement in preventive actions. Within the PROSELF framework, self-efficacy components such as mastery experience, feedback, and goal setting are applied uniformly across conditions, whereas HBM-related constructs (perceived severity, susceptibility, and cues to action) are emphasized mainly for cardiovascular and metabolic diseases, where risk perception has a stronger motivational value. This integration ensures that the intervention remains both theoretically grounded and adaptable to disease-specific behavioral determinants.

The study evaluates 12-month effects on global and domain-specific self-care and on secondary outcomes (adherence proxies, health-related quality of life, perceived social support), while identifying predictors of improvement.

The primary objective is to quantify changes in overall self-care at 12 months.

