### 2.3. Sample Size Justification

Using G*Power 3.1.9.7. (Heinrich-Heine-Universität Düsseldorf, Düsseldorf, Germany), we powered a repeated-measures ANOVA (within subjects, 4 timepoints). With effect size f = 0.25 (≈Cohen’s d = 0.5, moderate), α = 0.05, power = 0.80, and correlation among repeated measures r = 0.50, the minimum required sample is N = 159. Allowing for 15% attrition, we plan to recruit N = 180 (≈60 per diagnostic group), ensuring adequate precision for primary and secondary analyses.

The selected sample size (N = 180) ensures adequate precision for detecting moderate within-subject effects (Cohen’s d ≈ 0.5) across four timepoints, representing a balance between feasibility and statistical power. This sample is consistent with or larger than comparable nurse-led self-care intervention studies in chronic patients (typically N = 100–150) [19,20,21]. Given the multicenter design and inclusion of three major chronic conditions (COPD, diabetes, and CVD), the findings will allow reasonable generalization to similar community and primary-care populations within Southern Italy and comparable European settings.

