### 2.6. Instruments and Data Collection

We use validated instruments to capture global and disease-specific self-care, HRQoL, and social support. Administration occurs at T0, T1, T2, and T3 through encrypted forms; the platform enforces completeness checks, range validations, and time stamps. Nurse assistance is available for technical or comprehension issues.

**Self-Care of Chronic Illness Inventory (SC-CII)**. The SC-CII operationalizes Riegel’s theory across maintenance, monitoring, management (and confidence when applicable) as a trans-diagnostic measure [23]. Items are Likert-type; domain and total scores are standardized to 0–100 (higher = better self-care). The primary endpoint is the T0 → T3 change in total score, with domain-level analyses a priori. An increase of ≥8 points is considered clinically meaningful, consistent with the validation literature. Psychometrics across languages and Italian samples are robust (Cronbach’s α usually ≥0.80, test–retest ICC ≥ 0.75).

**Self-Care of Heart Failure Index (SCHFI, v7.x)**. Disease-specific self-care in HF, providing maintenance, management, and confidence scores, is standardized to 0–100 [24]. Psychometric testing has shown good reliability (Cronbach’s α = 0.76–0.90 across domains) and construct validity in multiple international validations, including the Italian version. Test–retest reliability was satisfactory (ICC > 0.70). While thresholds vary by study, values ≥ 70 are often interpreted as adequate self-care.

**Self-Care of Diabetes Inventory (SCODI)**. Targets T2DM self-care behaviors spanning adherence, lifestyle, and glucose self-monitoring, aligned with Riegel’s domains [25]. Scores are transformed to 0–100. The instrument demonstrates good internal consistency (Cronbach’s α = 0.80–0.88) and factorial validity in the Italian population, with acceptable test–retest reliability (ICC > 0.75).

**Self-Care of COPD Inventory (SCCOPD)**. Measures BPCO self-care (maintenance/monitoring/management), including medication routines, symptom recognition, and timely action [26]. Scores are transformed to 0–100. The SCCOPD has shown strong psychometric properties with Cronbach’s α = 0.83–0.89 and adequate construct validity in both English and Italian validations.

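### The primary endpoint is the 12-month change in SC-CII total, but the primary test asks about any difference among four timepoints and reaches the 12-month change only through a gate and a Bonferroni adjustment

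*Protocol article*

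**What the plan says.** Three places set one primary question.

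- Section 1 (Introduction): "The primary objective is to quantify changes in overall self-care at 12 months".
- Section 2.6, under the SC-CII: "The primary endpoint is the T0 → T3 change in total score, with domain-level analyses a priori".
- Section 2.7 repeats the outcome: "Change in SC-CII total (0–100) from T0 to T3 (12 months". It treats a rise of at least 8 points as clinically important.

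Section 2.8 (Statistical Analysis), under the primary analysis, sets a different test: "Within-subject change over time will be evaluated using repeated-measures ANOVA (or Friedman for non-normal data) on SC-CII total and domains". The step to individual timepoints follows: "When the omnibus test is significant, we will perform timepoint contrasts with Bonferroni-adjusted" p-values. T0 to T3 is not singled out among these contrasts, and their number is not given. On the choice between ANOVA and Friedman, the section says only: "Normality will be assessed with Shapiro–Wilk tests and Q–Q plots". The same paragraph promises: "We will report mean differences with 95% confidence intervals and effect sizes".

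Section 2.3 sizes the study for the omnibus test: "we powered a repeated-measures ANOVA (within subjects, 4 timepoints".

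**The concern.** A primary endpoint that is one contrast calls for a primary test of that contrast. The omnibus test answers a broader question: whether the mean differs anywhere among T0, T1, T2 and T3. Three consequences follow.

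1. **Wrong target.** A gain at 3 and 6 months that has gone by 12 months makes the primary test positive. This matters here because section 3 says the year-long programme is meant to outlast short-term motivational effects, so durability at 12 months is the claim at stake.
2. **Lost power.** A real 12-month change must first pass the omnibus test and then meet a reduced significance level.
3. **Data-dependent method.** If the data are judged non-normal, the primary p-value comes from a rank test. That p-value does not refer to the mean change, its confidence interval, Cohen's d or the 8-point threshold, which are the quantities the protocol uses to interpret the result.

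**Working it through.** **Inputs.** From section 2.3: four timepoints, r = 0.50, α = 0.05, power 0.80, f = 0.25 (d about 0.5), 15% attrition, 180 recruited. Completers: 180 × 0.85 = 153. Assumptions: two-sided contrasts, equal variances and correlations across visits, normal scores, and a contrast family of 3 (each visit against baseline) or 6 (all pairs). With r = 0.5 the SD of a T0 to T3 difference is √(2(1 − 0.5)) = 1 SD, so d and the paired effect size coincide.

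**The plan's own figure.** For the within-subject omnibus test, λ = f²·N·m/(1 − r) with df 3 and 3(N − 1). At N = 24, λ = 0.0625 × 24 × 4/0.5 = 12 and power is 0.817; at N = 23 it is 0.797. The stated inputs therefore give 24, not the stated 159. That is a separate matter and does not decide this point. What matters here is that the figure is said to refer to the omnibus test and not to the endpoint.

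**Positive primary test, no 12-month change.** Take means of 0, 0.3, 0.3, 0 SD at T0 to T3. The mean is 0.15 and Σ(μ − 0.15)² = 4 × 0.0225 = 0.09. Then λ = 153 × 0.09/0.5 = 27.5 with df 3 and 456, and omnibus power is 99.6%. A simulation of 40,000 trials gave 99.7% for ANOVA and 98.2% for Friedman. In the same trials the gated, Bonferroni-adjusted T0 to T3 contrast was significant in 1.7% (three contrasts) or 0.9% (six).

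**Power for T0 to T3.** The direct paired test has noncentrality d√N; at d = 0.25 this is 0.25 × √153 = 3.09, which gives 86.7%. The gated procedure was simulated for a profile rising to d at T3 (means 0, d/4, d/2, d):

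| True d at T3 | Direct, 0.05 | Gate + Bonferroni, 3 | Gate + Bonferroni, 6 |
|---|---|---|---|
| 0.20 | 69% | 47% | 41% |
| 0.25 | 87% | 71% | 65% |
| 0.30 | 96% | 88% | 84% |
| 0.50 | >99.9% | >99.9% | >99.9% |

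At d = 0.25, a change that appears only at T3, or that is present from T1 onward, gives 74% and 66% for the gated procedure, so the result depends little on the path. With the rising profile at d = 0.25, the direct test is significant and the omnibus test is not in 11% of trials; at d = 0.2 this is 16%.

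**Type I error.** With no change at any visit, the gated procedure declares a T0 to T3 change in 1.1% (three contrasts) or 0.7% (six) of trials, against 5% for a direct test. It is conservative.

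**Friedman branch.** The section names its diagnostics but gives no decision rule and does not say whether they apply to raw scores, differences or residuals. On normal data with the rising profile at d = 0.25, Friedman rejects in 65% of trials and ANOVA in 78%.

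**The case against.** The strongest reply is that the procedure works at the effect the study plans for. At d = 0.5 with 153 completers, power for T0 to T3 is above 99.9% even with six contrasts. That stands. The loss matters for effects of about 0.3 SD or less. Section 2.7's 8 points cannot be placed on this scale because no SD is given: 8 points is d = 0.5 if the SD is 16, and d = 0.25 if it is 32.

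The second reply is that the planned contrasts catch a transient gain, since the follow-up T0 to T3 comparison would usually be non-significant. This also stands. A false 12-month claim would require reading the omnibus result alone. But the omnibus test is the one the protocol puts first under its primary analysis, and nothing says that T0 to T3 decides the result.

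Several stronger readings are tempting, and the document does not support them.

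- A reader might infer that the mean 12-month change may never be estimated. Section 2.8 promises mean differences with confidence intervals and does not restrict them to the ANOVA branch. It also does not say that they will be given when the omnibus test is not significant.
- A reader might infer that the switch to Friedman is almost certain for a bounded score. That depends on an assumed score shape and on which quantity is tested, and Q–Q plots are used alongside the formal test.
- A reader might infer that everyone with a missed visit is lost. Section 2.8 plans multiple imputation if data are missing at random, with complete cases as a sensitivity comparison.
- The lack of a nurse or centre term is a separate modelling question that an article can leave to a fuller analysis plan.

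**Conclusion.** The point holds as a mismatch between endpoint and test. It rests on what section 2.8 states, not on missing detail: a later analysis plan would have to override the stated primary analysis to remove it.

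The wrong target is the main defect and does not depend on the planned effect size: under an early gain that is fully lost, the primary test is positive in over 99% of trials. The power loss is secondary. At d = 0.25 it is about 13 to 16 percentage points with three contrasts and 20 to 22 with six, and at d = 0.5 it is negligible. It would be wrong to conclude that false positives are inflated or that the study is underpowered for T0 to T3 at its planned effect.

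The figures assume 153 completers, r = 0.5, equal variances and normal scores; the transient profile is illustrative. The objection to the Friedman branch needs no figure: the primary method is chosen from the data by an unstated rule, and a rank p-value does not match the mean-scale quantities the protocol reports.

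**What to change.** In section 2.8, name the T0 to T3 contrast in SC-CII total as the single primary test, at two-sided 0.05, not gated by the omnibus test and not Bonferroni-adjusted. Report the mean change with its 95% CI whatever the omnibus result. A paired contrast on the multiply imputed data would do; so would the same contrast from a mixed model.

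Make the omnibus test, the other timepoints and the three domains secondary, with a stated contrast family and multiplicity adjustment. Remove the normality-triggered switch and use rank or robust methods as sensitivity analyses only.

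Restate section 2.3 for the T0 to T3 contrast. With r = 0.5, 80% power needs 34 completers at d = 0.5, 90 at 0.3, 128 at 0.25 and 199 at 0.2.

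The cost is wording: no visits, instruments or participants are added. The omnibus test loses its primary status and the power statement must be rewritten. At submission, ethics approval was pending (section 2.11) and registration, including the analysis plan, was still to come (section 2.13), so the change can be made before any data exist.

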Secondary objectives are (i) to assess changes across maintenance, monitoring, and management domains; (ii) to evaluate the effects of nurse-led digital education on treatment adherence, health-related quality of life, and perceived social support; and (iii) to identify predictors of improvement and patient engagement during follow-up.

Research hypotheses are integrated with these objectives. Specifically, we hypothesize that

(1)Participation in the PROSELF program will significantly improve self-care maintenance, monitoring, and management behaviors over time (linked to the primary objective i);(2)Nurse-led digital educational interventions will enhance adherence and perceived self-efficacy (linked to secondary objective ii);(3)Improvements in self-care and adherence will be associated with a higher quality of life and stronger perceived social support at 12 months (linked to secondary objective iii).

These hypotheses will be tested using validated self-care, quality-of-life, and social-support measures, as detailed in Section 2.

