### 2.5. Intervention

The PROSELF intervention is a nurse-led, theory-based digital program delivered via encrypted video calls and supported by asynchronous materials (brief videos, PDFs, checklists, reminders). Each session lasts 30–40 min and is individualized through shared agenda setting and goal planning. Content maps directly onto maintenance, monitoring, and management, integrating Bandura’s Self-Efficacy (mastery, vicarious experiences, persuasion, and emotional regulation) and Health Belief Model constructs (perceived risk, benefits, barriers, and cues to action).

Session 1: (T0, baseline; focus: maintenance). Disease education; medication routines; nutrition and physical activity; identification of personal goals; and barrier mapping with concrete strategies.Session 2: (T1, 3 months; focus: monitoring). Symptom perception and interpretation; home tracking (glycemia, SpO_2_, peak flow, and blood pressure as relevant); warning signs and thresholds; digital logs; and feedback on data quality.Session 3: (T2, 6 months; focus: management). Action plans for symptom exacerbations; problem solving; when/how to contact providers; aligning self-management actions with care plans; and relapse prevention.Session 4: (T3, 12 months; focus: reinforcement and consolidation). Review of progress; consolidation of habits; prevention of regression; update of personal action plans; and refreshing digital literacy.

All sessions are delivered on a GDPR-compliant platform with appointment reminders and secure authentication. Between visits, patients receive brief cues to action (SMS/email reminders) and links to concise educational resources aligned with international clinical guidance (e.g., GOLD for COPD; ADA standards for diabetes; and ESC guidance for CVD) to reinforce self-efficacy and adherence to the agreed goals.

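### The predictor regression lists the baseline score as a predictor of change, where its coefficient mainly reflects regression to the mean, and mixes in post-baseline engagement that is open to reverse causation

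*Protocol article*

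**What the plan says.** Section 2.8 (Secondary analyses) states: "Multivariate linear regression will explore predictors of 12-month improvement (ΔSC-CII total". Age, sex, education and diagnosis are listed as predictors, together with "baseline score, and digital engagement metrics (attendance, completion time, and message interactions". All enter one model, and no time window is set for the engagement metrics.

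The model serves secondary objective (iii) in the Introduction, "to identify predictors of improvement and patient engagement during follow-up". Section 2.5 places the last session at the outcome visit: "Session 4: (T3, 12 months; focus: reinforcement and consolidation". Table 2 likewise puts the final session and the final evaluation at T3. Section 2.11 allows sessions to be stopped or moved when a patient's condition worsens or the patient is admitted to hospital. Section 2.9 names worsening health among the possible reasons for leaving the study.

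The Strengths and Limitations section accepts that having no control group limits causal inference, but cites multivariate modelling in support of the study's real-world evidence. Nothing in the article says how the baseline or engagement coefficients are to be read.

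**The concern.** There are two separate problems in one model.

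**Baseline score.** The outcome is T3 − T0, and T0 is also a covariate. Patients who score low at T0 partly by chance tend to score closer to the mean at T3, whatever the programme does. A negative coefficient is therefore expected without any differential benefit, and no control group is available to show how much of it is regression to the mean.

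**Engagement.** Attendance, completion time and messages build up during follow-up. A patient who deteriorates may miss or postpone sessions and also score lower at T3. A generally conscientious patient may both engage more and score higher. Either would make engagement look beneficial. In addition, if age, education or diagnosis acts partly through engagement, holding engagement fixed removes that part of their association.

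At stake is the answer to objective (iii): which patients improve, and whether engagement is what helps.

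**Working it through.** **Inputs from the protocol**
- Section 2.3: "correlation among repeated measures r = 0.50", used here as the T0–T3 correlation r.
- Section 2.3: 180 recruited with 15% attrition, so 180 × 0.85 = 153 completers.
- Section 2.6: "test–retest ICC ≥ 0.75". Its floor is borrowed as a higher scenario, r = 0.75. This is an assumption, because a short-term reliability is not a 12-month correlation.
- Two-sided 0.05 is assumed for the regression; its level is not stated.

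The article gives no figure for this model. Its "the minimum required sample is N = 159" concerns the repeated-measures ANOVA and is not used here. That figure does not reproduce under the stated inputs: the noncentral F with λ = f²Nm/(1−r) and m = 4 gives 24. That is a separate matter.

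**Step 1: baseline coefficient with no differential benefit**

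Slope of (T3 − T0) on T0 = r × SD3/SD0 − 1. With SD3 = SD0 this is −(1−r), R² = (1−r)/2, and t = −(1−r)/√[(1−r²)/(n−2)].

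| r | slope | R² | t at n = 153 | simulated rejection |
|---|---|---|---|---|
| 0.50 | −0.50 | 0.25 | −0.50/√(0.75/151) = −7.1 | 100% |
| 0.75 | −0.25 | 0.125 | −0.25/√(0.4375/151) = −4.6 | 99.6% |
| 0.90 | −0.10 | 0.05 | −0.10/√(0.19/151) = −2.8 | 79% |

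The simulation fitted the stated covariates with one engagement metric, and neither baseline nor engagement affected true change. If multiple imputation retains all 180, t is −7.7 at r = 0.50 and −5.0 at r = 0.75.

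At a slope of −0.50, a patient starting 16 points lower is predicted to gain 0.50 × 16 = 8 points more. That equals the protocol's threshold for a clinically important change and arises from the artefact alone.

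**Step 2: sensitivity to the SD**

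Suppose SD3/SD0 = 1.2 (assumed), with r unchanged.
- r = 0.50: slope = 0.60 − 1 = −0.40, t = −0.40/(1.2 × 0.0705) = −4.7.
- r = 0.75: slope = 0.90 − 1 = −0.10, t = −0.10/(1.2 × 0.0538) = −1.5.

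The negative slope is likely, but neither its size nor its significance is guaranteed.

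**Step 3: T3 or change as outcome**

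If T3 − T0 = a + b·T0 + c·X, then T3 = a + (b+1)·T0 + c·X with the same residuals. The T0 coefficient moves by exactly +1 (−0.50 becomes +0.50), and every other coefficient and p-value is unchanged.

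**Step 4: engagement with no true effect (n = 153)**

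False-positive rates by the assumed source of the link. None of these correlations is in the documents.

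| Link | Correlation | r = 0.50 | r = 0.75 |
|---|---|---|---|
| None, or only with observed T0 score | – | 5.5–5.8% across scenarios | (same range) |
| With a stable self-care trait | 0.1 / 0.2 / 0.3 / 0.5 | 8.5 / 16 / 33 / 75% | 7.5 / 12 / 23 / 59% |
| With the visit-specific deviation at T3 (reverse causation) | 0.1 / 0.2 / 0.3 | 16 / 50 / 85% | 15 / 44 / 78% |

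In a further simulation at r = 0.50, an unmeasured deterioration factor correlated −0.2, −0.3 or −0.4 with both engagement and the T3 score. Rejection was 9%, 26% and 63%.

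**The case against.** **Baseline belongs in the model.** This stands in full. Step 3 shows that including T0 makes the change model equivalent to an analysis of covariance for every other covariate. The fault is confined to presenting T0 as one of the predictors of improvement. The protocol also nowhere claims that low scorers benefit most; it only leaves that reading open.

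**The negative slope is not a certainty.** This stands too. Section 2.2 excludes patients with near-optimal self-care, so a smaller SD at T0 than at T3 is plausible, and Step 2 shows what that can do.

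**A reader might infer that the model will report engagement as a predictor even when it has no effect.** The documents do not support that. Without a shared trait or reverse causation the error rate stays near 5%, and regressing change on baseline does not create the engagement problem. What the documents do support is a plausible route: sessions may be stopped or moved on worsening, no listed covariate measures worsening, and one session coincides with the outcome visit. That session 4 counts towards attendance is the natural reading, but it is not stated.

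**A reader might also infer that objective (iii) contradicts the model**, because engagement could be read there as something to be predicted. The wording is ambiguous, and a variable may be an outcome in one analysis and a covariate in another. A separate model for predictors of engagement is detail that an analysis plan may supply.

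**The analysis is exploratory and the causal limits are conceded.** That reduces the weight of the point. However, identifying predictors is a named secondary objective, and the general caveat addresses neither coefficient.

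**Conclusion.** The point holds in a limited form. For baseline, the model as specified is very likely to return a significant negative coefficient with no differential benefit: −0.50 (t about −7.1) at the protocol's own r, and −0.25 (t about −4.6) at r = 0.75. This assumes equal variances and 153 completers, and it weakens at r near 0.9 or if the SD rises by T3. Without a control group the coefficient is not evidence that low-baseline patients gain more.

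For engagement, the bias is possible and has a mechanism in the protocol, but its size is unknown. The false-positive rates in Step 4 illustrate assumed links and are not predictions for this study.

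The issue concerns one exploratory secondary regression. The primary endpoint and its test are untouched, so it should be corrected but is not critical.

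**What to change.** 1. Fit the predictor model with baseline variables only. Keep T0 SC-CII as an adjustment covariate and state that its coefficient will not be interpreted as a predictor of improvement. Either T3 or the change may be the outcome; changing from one to the other solves nothing by itself.
2. Analyse engagement in a separate model that uses only engagement recorded before T3, leaves out session 4, and adjusts for T0 SC-CII. Report it as association only.
3. Treat any further adjustment for T2 SC-CII as a sensitivity analysis. Earlier engagement probably acts partly through self-care at T2, so conditioning on it could remove a real benefit.

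The cost is a few lines of text and one additional small model. Late engagement goes unused, and confounding by a shared trait remains, because a time limit removes only the overlap with the outcome visit.

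### The planned 5 to 10 imputations are an open, low range that leaves near-threshold p-values dependent on the random seed; one larger fixed number would cure this at almost no cost (minor)

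*Protocol article*

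**What the plan says.** Under Missing data, Section 2.8 makes imputation conditional on the missingness mechanism ("If data are missing at random, we will apply multiple imputation") and sets its size as "multiple imputation (m = 5–10 datasets), including all variables used in the analysis models". It adds a robustness check: "Sensitivity analyses will compare imputed vs. complete-case results to assess robustness".

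The analyses to be run are listed in the same section. The primary one is "repeated-measures ANOVA (or Friedman for non-normal data) on SC-CII total and domains". Follow-up comparisons are conditional ("When the omnibus test is significant, we will perform timepoint contrasts with" Bonferroni adjustment), and the plan also states: "We will report mean differences with 95% confidence intervals and effect sizes". Analogous models are applied to the disease-specific self-care scales, EQ-5D-5L, SF-36 and MSPSS.

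Section 2.3 gives the expected loss ("Allowing for 15% attrition"), a planned sample of 180 with about 60 per diagnosis, and a correlation among repeated measures of 0.50.

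**The concern.** Multiple imputation draws random values, so the pooled estimate, its standard error and its p-value all carry Monte Carlo error. That error shrinks as the number of imputations m grows. With m at 5 to 10, two analysts who use the same data and the same imputation model but different seeds can obtain visibly different p-values. Because m is a range, the analyst can also choose it after seeing results.

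This does not bias the estimate and costs little precision. What is at stake is reproducibility for results near a cut-off. Section 2.8 has several cut-offs: the omnibus test that gates the contrasts, the Bonferroni-adjusted contrasts, and the tests on the domains and secondary scales.

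**Working it through.** The plan offers no derivation of m, so there is no figure of its own to reproduce. The check is what 5 to 10 imputations imply at the planned attrition.

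**Inputs from Section 2.3.** N = 180; attrition 15%, so 180 × 0.15 = 27 lost and 153 remaining; correlation 0.50; planned effect d about 0.5.

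**Assumptions, not in the documents.** Multivariate normal scores, equal correlation between all visits, and monotone dropout spread evenly over the three follow-up visits. The fraction of missing information (FMI) for the T0 to T3 mean difference came out at about 0.17 in this simulation. It was about 0.10 in a second simulation with slightly different correlations and all losses at T3. A dropout of 30% was added as a stress case.

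**Step 1. Efficiency.** Relative efficiency = 1 / (1 + FMI/m).
- FMI 0.10: 1/(1 + 0.10/5) = 0.980; 1/(1 + 0.10/10) = 0.990.
- FMI 0.17: 1/(1 + 0.17/5) = 0.967; 1/(1 + 0.17/10) = 0.983.

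The loss is about 1 to 3%, so precision is not the problem.

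**Step 2. Seed-to-seed variation in the test statistic.** The standard deviation of the pooled z across seeds is about √(FMI/m).

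| m | FMI 0.10 | FMI 0.17 |
|---|---|---|
| 5 | 0.141 | 0.184 |
| 10 | 0.100 | 0.130 |
| 50 | 0.045 | 0.058 |
| 100 | 0.032 | 0.041 |

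As a rough guide, put z at 1.96 and move it by ±1.96 × 0.184 (m = 5, FMI 0.17). This gives z from 1.60 to 2.32, or p from 0.110 to 0.020. With m = 100 the same step gives p from 0.060 to 0.041.

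**Step 3. Simulation.** One incomplete dataset was held fixed and re-imputed with 1,000 sets of imputations at each m. The T0 to T3 mean difference was pooled by Rubin's rules with small-sample degrees of freedom. The dataset was shifted so that its p-value with many imputations was about 0.05. The table gives the 2.5th to 97.5th percentile of p across seeds.

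| m | 15% dropout | 30% dropout (stress case) |
|---|---|---|
| 5 | 0.016–0.146 | 0.011–0.195 |
| 10 | 0.023–0.091 | 0.017–0.129 |
| 50 | 0.034–0.065 | 0.030–0.075 |
| 100 | 0.038–0.058 | 0.034–0.064 |

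The simulated ranges at m = 5 are wider than the Step 2 guide because the estimated between-imputation variance and the degrees of freedom also change with the seed.

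For a dataset with a large-m p of about 0.03 at 15% dropout, the result is non-significant at 0.05 for 21% of seeds with m = 5, 9.5% with m = 10, 2% with m = 20 and none with m = 50.

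**Step 4. The plan's other cut-offs.** If all six visit pairs are compared (an assumption), the Bonferroni threshold is 0.05/6 = 0.0083. For a dataset placed at that threshold, p ranges over 0.002–0.041 with m = 5 and 0.003–0.025 with m = 10. An omnibus F test pooled by the D2 rule, in the dataset whose T0 to T3 p is about 0.05, gave p of 0.029–0.184 with m = 5, 0.034–0.115 with m = 10 and 0.048–0.078 with m = 50.

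**Step 5. Which results could lie near a cut-off.**
- Primary effect at d = 0.5: with 153 patients and correlation 0.50, the SD of change equals the SD of the score, because √(2(1 − 0.50)) = 1. The standard error is 1/√153 = 0.081 SD and 0.5/0.081 is about 6.2. In the simulated dataset, 0.5/0.0735 = 6.8. No seed changes that conclusion.
- Disease-specific scale: 60 × 0.85 = 51 patients, standard error 1/√51 = 0.14 SD. An effect of d = 0.28 sits at z = 2, and d = 0.37 sits at the 0.0083 threshold (2.64 × 0.14). Such effects are plausible.

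**The case against.** The strongest reply is that the problem exists only close to a threshold. For a dataset lying exactly there, two analysts would disagree about half the time, but few datasets do. Convert the 15% dropout ranges in Step 3 to a standard deviation of z (0.244 at m = 5, 0.149 at m = 10) and average over sampling variation. Disagreement at the 0.05 level then occurs in at most about 11% of studies with m = 5 and 7% with m = 10, and those maxima need a true effect exactly at the threshold. With no effect the figures are about 3% and 2%; at d = 0.5 they are zero. This stands, and it is why the point is minor. The corresponding maxima with 50 and 100 imputations are about 3% and 2%.

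It can also be said that a journal article leaves the seed and the pooling rule to a full protocol or analysis plan. That stands for those omissions. It does not cover the range of 5 to 10, which the article states itself.

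Three stronger readings are tempting and are not supported:
- **That the imputed result has no defined form,** because the primary test is "repeated-measures ANOVA (or Friedman for non-normal data") and partial eta-squared is reported. Section 2.8 also promises mean differences with confidence intervals, which Rubin's rules pool directly. F and chi-square statistics can be combined by D1- or D2-type rules. Only partial eta-squared lacks a standard pooled form, and it is descriptive.
- **That some imputed datasets would go to ANOVA and others to Friedman.** Nothing says normality will be judged separately in each imputed dataset.
- **That the complete-case analysis would needlessly drop patients who have T0 and T3 but miss a middle visit.** The article does not define a complete case or give a rate of intermittent missed visits. Under dropout alone, everyone seen at T3 has the earlier visits.

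**Conclusion.** The concern holds as a minor point about reproducibility. An unfixed m between 5 and 10 lets the seed and the choice of m move a p-value of about 0.05 anywhere from roughly 0.02 to 0.09 (m = 10) or 0.02 to 0.15 (m = 5) at the planned attrition. The estimate itself loses only 1 to 3% in efficiency, and the primary conclusion at the planned effect is not at risk. The exposed results are the SC-CII domains, the disease-specific scales, EQ-5D-5L, SF-36 and MSPSS, and only where they fall near a cut-off.

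The sizes rest on normal scores, equal correlations of 0.50 and even monotone dropout. A higher fraction of missing information widens them, as the 30% case shows; a lower one, such as 0.10, narrows them.

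**What to change.** In Section 2.8, replace the range with a single pre-specified number of imputations, at least 50 and for example 100, and state that the random seed will be fixed and recorded. The simulation supports 50 as adequate; 100 narrows the range a little further.

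It would help to add that the T0 to T3 mean difference with its 95% confidence interval, pooled by Rubin's rules, is the imputed result. The plan already reports that quantity, so no analysis is added.

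The cost is one or two sentences and minutes of computing. Section 2.11 says no data collection starts before ethics approval, which was pending at submission, and the data availability statement says no dataset exists yet. On that footing the change can be made before any result is known.
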